# Effect of spinal orthosis on clinical outcomes of patients after oblique lumbar interbody fusion: a randomized controlled trial study protocol

**DOI:** 10.1186/s13063-023-07796-x

**Published:** 2023-12-04

**Keywords:** Oblique lumbar interbody fusion, OLIF, Spinal orthosis, Lumbar minimally invasive surgery, Clinical efficacy

## Abstract

**Background:**

Oblique lumbar interbody fusion (OLIF) is an internationally popular minimally invasive technology for the treatment of various lumbar diseases. Since its introduction to China in 2014, OLIF technology has clearly shown its superiority in reconstructing intervertebral stability, restoring intervertebral space height, achieving indirect decompression, and restoring normal lumbar sequence. However, some patients still suffer from persistent symptoms after OLIF, including low back pain and soreness, which indirectly affect the overall surgical efficacy and patient satisfaction. Therefore, some clinicians recommend that patients routinely use spinal orthoses after OLIF to reduce the stress on the lower back muscles and ligaments, thereby relieving or avoiding postoperative residual symptoms or new symptoms. Accordingly, spinal orthosis use after OLIF has emerged as an essential option. However, the role of spinal orthoses in OLIF and their specific impact on postoperative patient clinical outcomes have remained unclear, and there is a lack of strong clinical evidence to indirectly or directly support the role of spinal orthoses in OLIF and demonstrate their impact on patient clinical outcomes. This study aims to investigate the role of spinal orthoses in OLIF by grouping patients based on the use or nonuse of spinal orthosis after OLIF, thus providing a better basis for the majority of patients and physicians.

**Methods/design:**

We plan to conduct a 1-year randomized controlled trial involving 60 subjects. The subjects will be randomized into two groups: group A (those wearing spinal orthoses after surgery) and group B (those not wearing spinal orthoses after surgery). The clinical outcomes of these patients will be evaluated using the Oswestry disability index, visual analog scale, and Brantigan, Steffee, Fraser 1 day before surgery and 2 weeks and 1, 6, and 12 months after surgery.

**Discussion:**

This randomized controlled trial aims to provide a reference for further comprehensive trial design. The findings of this study will provide a better and more scientific basis for the choice of postoperative rehabilitation and treatment for patients undergoing such a procedure.

**Trial registration:**

This study has been registered in the Chinese Clinical Trial Registry (Registration No.: ChiCTR2200059000). Registration date: April 22, 2022.

Registration website: http://www.chictr.org.cn/showproj.aspx?proj=166310

**Supplementary Information:**

The online version contains supplementary material available at 10.1186/s13063-023-07796-x.

## Background

Oblique lumbar interbody fusion (OLIF) is an innovative minimally invasive technology to treat various lumbar spine diseases, which was first proposed by Mayer in 1997 [1]. It has not been widely applied due to the limitation of supporting devices and cages, until 2012, when [name] modified and developed a special fusion cage and its supporting access system based on the original transforaminal lumbar approach interbody fusion cage. OLIF technology does not destroy the posterior muscles, ligaments, or other structures, thus reducing the risk of postoperative low back pain, and also enables direct removal of a large number of diseased intervertebral disc tissues, thus allowing a cage with a larger contact area, which can greatly increase the support strength provided by the cage [2] and increase the success rate of fusion. Therefore, OLIF technology is recommended for various lumbar diseases that require intervertebral stability reconstruction, restoration of interbody height, interbody decompression, and restoration of normal lumbar sequences.

According to the recommendations of the Clinical Application Guidelines for Lumbar Oblique Lateral Interbody Fusion [3] of the Spine Surgery Group of the Chinese Orthopedic Association, the OLIF technology is intended for lumbar spinal stenosis and lumbar degenerative scoliosis based on imaging, correction of lumbar anterior lordosis in combination with posterior internal fixation, segmental instability and I degree lumbar spondylolisthesis, II degree lumbar spondylolisthesis, adjacent vertebral disease after lumbar fusion, and discogenic low back pain. However, it is not recommended for spinal stenosis caused by nucleus pulposus prolapse, fat deposition or other space-occupying factors, congenital spinal stenosis, bony spinal stenosis caused by calcification of the ligamentum flavum, or spinal stenosis caused by bony fusion of the posterior facet joints [4]. From the above indications and contraindications, it can be noted that OLIF technology is a classic and effective approach to treat spinal instability diseases [5–9]. OLIF technology has been compared with classical surgical methods such as transforaminal lumbar interbody fusion, anterior lumbar interbody fusion, and posterior lumbar interbody fusion in previous studies, and it was found that OLIF technology was superior in shortening the hospitalization time, reducing blood loss and postoperative low back pain, and restoring intervertebral space height and segmental lordosis [10–13]. With the continuous development of OLIF technology, the in-depth study of anatomy [14, 15], and based on a summary of clinical experience, the spine surgery team of the Affiliated Hospital of Zhejiang University in China modified the original OLIF surgical approach and proposed the anterior-inferior psoas (AIP) exposure technology [16, 17]. AIP technology, as a localized improvement of OLIF technology, reduces the risk of OLIF and makes the OLIF technology simple and clear, and is more suitable for Chinese patients, thus further promoting the wide clinical application of OLIF technology.

It is well established that any type of surgery is a form of trauma for human beings, regardless of the size of the trauma, but it is also likely to cause damage, and some such damage is even harmful. Despite many advantages of OLIF in lumbar spine surgery, it is also an invasive operation for the body, which may lead to residual symptoms or new complications in some patients after surgery and may indirectly increase the rate of lumbar reoperation and reduce the effect of surgery [18]. Therefore, it is imperative to adopt other means after lumbar surgery to reduce residual symptoms and postoperative complications. The commonly used clinical approaches include prolonged bed rest after surgery, avoidance of labor, lifting heavy articles, and prolonged standing or sitting and wearing a spinal orthosis. A better and commonly used clinical method to avoid reducing the quality of life of patients after surgery is to wear a spinal orthosis routinely after surgery.

Generally, fixation of any musculoskeletal injury is favorable for reducing the pain after injury [19]. Therefore, spinal orthoses can be used not only to relieve residual back pain symptoms [20] but also for postoperative rehabilitation of patients after lumbar spine surgery [21]. The use of spinal orthosis after OLIF is to fix the entire body movement [22] and the motion segment, relieve muscle strength [23], reduce pain [24], enhance the fusion rate [25], and improve the functional prognosis [26]. However, it is undeniable that non-standard or the wearing of spinal orthoses not for the prescribed time after surgery may also lead to muscle atrophy [27], skin irritation, delayed recovery, and other side effects.

For this reason, although the spinal orthosis exhibits some advantages after lumbar fusion, the necessity of its clinical use has been questioned due to its limitations. Additionally, the role of postoperative orthoses in OLIF has not been determined, and there is a lack of strong evidence to prove any correlation between the routine use of orthoses after OLIF and the final clinical outcome of patients. Therefore, we plan to conduct a randomized trial to evaluate the necessity of using lumbar orthoses after OLIF for postoperative adjuvant therapy in such patients.

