### Assumption

It is assumed that the clinical outcome of patients wearing spinal orthoses after OLIF is superior to that of patients in the control group.

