### Sample size

Because this study is based on clinical application, it is difficult to calculate the sample size through pre-experiments according to the actual situation; thus, the sample size of this study was finally determined based on the previous relevant literature data. The sample size outcome effect size was obtained from the literature using the ODI and VAS scores [29]. The mean change of the ODI in group A was approximately 92%, and the mean change of the VAS was approximately 0–3 points, while the mean change of the ODI in group B was approximately 85%, and the mean change of the NRS was approximately 4–5 points. The sample size was calculated using the sample size formula of the quantitative equivalence experiment *n* = 2(*Z*_*α*_ + *Z*_*β*_)^2^*δ*^2^/(*D* − *Δ*)^2^, assuming that *α* = 0.05 and *D* = 2.09 − 1.45 = 0.64, *δ*^2^ = [(0.56 + 0.78)/2]^2^ = 0.46 was obtained from literature retrieval, different values of *β* and superiority bounds were selected to calculate the sample size matrix, as shown in Table 1, and finally *n* = 50 was selected; taking into consideration a 20% dropout, thus 30 cases should be enrolled to each group, a total of 60 cases in two groups.

**Table 1 Tab1:** Sample size matrix

*α*	*β*	*D*	*δ*^*2*^	*Δ*	*n*
0.05	0.2	0.64	0.46	0.2	38
0.05	0.2	0.64	0.46	0.3	63
0.05	0.1	0.64	0.46	0.2	50
0.05	0.1	0.64	0.46	0.3	84

This trial is to be conducted in the Second Spine Department of the Fourth Clinical Medical School of Xinjiang Medical University, and hospitalized patients who meet the inclusion criteria will be included in the study. Because of the large number of patients undergoing OLIF in this department, it is possible to recruit sufficient subjects within the prescribed time; thus, an insufficient sample size is highly unlikely. In addition, there are benefits for patients participating in the study to supplement the sample size (e.g., free professional consultation, postoperative functional exercise instruction, and postoperative care consultation).

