## Discussion

According to previous studies and clinical experience, spinal orthosis is commonly used after open lumbar fusion. However, as previously reported, there is insufficient evidence to systematically prove the necessity of using spinal orthoses after lumbar spine surgery [32]. Obviously, there is a clear lack of consensus on the indications for routine spinal orthosis use after lumbar spine surgery.

For lumbar fusion, the benefits of postoperative bracing are intensively debated. In clinical practice, due to the absence of scientific guidelines, some physicians often subjectively choose whether to use a spinal orthosis after OLIF surgery based on their own experience. This subjectivity may increase the possibility of some unnecessary risks, indirectly leading to undesirable outcomes and increasing uncertainty about prognosis, and may also increase the pain and economic burden of patients.

Patients who use spinal orthoses after surgery may feel more comfortable and, thus, move more easily under ordinary circumstances. However, there are no definitive findings on whether routine spinal orthosis use after surgery leads to any negative effects and thus adversely affects the final outcome. Accordingly, we have designed this study to prove whether routine spinal orthosis use in patients after OLIF has an impact on their clinical outcomes, so as to provide a more scientific basis for clinicians on deciding on its use.

Clearly, this study has some limitations. The clinical outcome evaluation indexes are relatively single, and the follow-up time is relatively long, which may lead to problems such as a reduced reliability of some data. Therefore, the data are collected in strict accordance with the requirements during the study, and the relevant factors affecting the experimental data are minimized and the existing limitations will be further improved in the future research process.

To our knowledge, this study is the first prospective randomized trial to evaluate the effect of spinal orthosis on postoperative clinical outcomes in patients undergoing OLIF, thus providing clinicians and patients with a more scientific treatment choice.

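### The sample-size formula is labelled equivalence but sizes superiority by a margin, while the stated hypothesis has no margin and the stated aim is necessity, which a null result here could not settle

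*Protocol article*

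**What the plan says.** Four places in the protocol article describe what the trial is to show.

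- **Background, last paragraph:** "we plan to conduct a randomized trial to evaluate the necessity of using lumbar orthoses after OLIF for postoperative adjuvant therapy in such patients".
- **Assumption:** the hypothesis is that "the clinical outcome of patients wearing spinal orthoses after OLIF is superior to that of patients in the control group". No margin is named.
- **Sample size:** "The sample size was calculated using the sample size formula of the quantitative equivalence experiment". The same sentence goes on to say that "superiority bounds were selected to calculate the sample size matrix". Table 1 uses Δ = 0.2 or 0.3 with D = 0.64 and variance 0.46. The chosen n = 50 is the row with β = 0.1 and Δ = 0.2. Enrolment is 30 per group with a 20% dropout allowance.
- **Discussion:** "we have designed this study to prove whether routine spinal orthosis use in patients after OLIF has an impact on their clinical outcomes".

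The Sample size section does not say which outcome the 0.64 belongs to, or which sign is favourable.

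**The concern.** Plain superiority, superiority by more than a margin, and equivalence have different null hypotheses and different success rules. The Sample size section names the third and computes the second; the Assumption section states the first. A result can then succeed under one section and fail under another.

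Necessity is a further step. A superiority trial that misses its criterion has not shown that the treatment can be left out. The Discussion wants the results to help clinicians decide on brace use, so what a non-significant result may be taken to mean bears directly on practice.

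**Working it through.** **Inputs (Sample size section and Table 1).** D = 2.09 − 1.45 = 0.64; variance 0.46; α = 0.05; β = 0.1 or 0.2; Δ = 0.2 or 0.3; 30 enrolled per group; 20% dropout, so 30 × 0.8 = 24 completers per group. I take a positive difference to favour the orthosis, because the section does not say.

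**1. Reproducing Table 1.** n = 2(Zα + Zβ)² × variance/(D − Δ)², with two-sided α (Zα = 1.960):

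| β | Δ | D − Δ | n unrounded | n | Table 1 |
|---|---|---|---|---|---|
| 0.2 | 0.2 | 0.44 | 37.30 | 38 | 38 |
| 0.2 | 0.3 | 0.34 | 62.47 | 63 | 63 |
| 0.1 | 0.2 | 0.44 | 49.93 | 50 | 50 |
| 0.1 | 0.3 | 0.34 | 83.62 | 84 | 84 |

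All four rows match. One-sided α would give 30, 50, 41 and 69, which do not.

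**2. What the formula tests.** The effect to be detected is the excess of D over Δ, so the null hypothesis is a difference of at most Δ. That is superiority by a margin. An equivalence calculation assumes a true difference inside the equivalence region, and 0.64 lies outside both ±0.2 and ±0.3.

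**3. Where the two superiority rules part.** SE = √(2 × 0.46/n); half-width = t(0.975) × SE.

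| Per group | SE | 95% half-width | Observed difference needed, no margin | Observed difference needed, Δ = 0.2 |
|---|---|---|---|---|
| 30 | 0.175 | 0.351 | 0.35 | 0.55 |
| 24 | 0.196 | 0.394 | 0.39 | 0.59 |

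An observed difference between 0.35 and 0.55 (30 per group) meets the Assumption section's hypothesis and fails the one used for sizing.

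**4. Power if the true difference is 0.64.** Normal approximation: power = Φ((0.64 − bound)/SE − 1.96).

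- No margin, 24 per group: Φ(0.64/0.196 − 1.96) = 0.905.
- No margin, 30 per group: Φ(0.64/0.175 − 1.96) = 0.955.
- Δ = 0.2, 24 per group: Φ(0.44/0.196 − 1.96) = 0.613.
- Δ = 0.2, 30 per group: Φ(0.44/0.175 − 1.96) = 0.710.

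The 90% of the chosen row needs 50 analysed per group, because the factor 2 makes n a per-group number. The figure of 30 per group follows only if 50 is read as the total: 50/2 × 1.2 = 30.

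**5. What a null result could exclude.**

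- With an observed difference of exactly 0, the 95% interval is ±0.35 (30 per group) or ±0.39 (24). It excludes 0.64, but not a benefit above 0.2 or 0.3, the plan's own bounds.
- With an observed difference of 0.30 and 24 per group, the interval is 0.30 ± 0.394, or −0.09 to 0.69. It contains both zero and the full assumed effect.
- If the true difference were 0.4 with 24 per group, plain superiority would be missed with probability 1 − Φ(0.4/0.196 − 1.96), about 47%. Superiority by 0.2 would be missed about 83% of the time.

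**The case against.** The best defence is that there is only one claim. The Assumption section says superiority, the Sample size section calls Δ a superiority bound, and the formula agrees. Equivalence is then one wrong word, and necessity is motivational language at the end of an introduction. The Methods/design section gives a neutral aim of comparing effects, and the abstract claims only to inform a fuller trial. Decision rules and the reporting of a non-significant result are often left to an analysis plan that is not shown here.

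Much of this stands. Equivalence is best read as a mislabel and not as a second objective. A reader might infer that a null result will be reported as showing the brace unnecessary, but no section says so; that is inference from the necessity wording. A reader might also infer that the trial claims equivalence and must fail, since the 90% interval at 30 per group (±0.29) is wider than ±0.2. The protocol sets no equivalence margin, so that argument tests an objective it never adopted.

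Two things survive. The label and the mismatch over the margin are contradictions within the article itself, not omissions that an analysis plan would fill. Reading everything as superiority still leaves two hypotheses whose power at this size differs by about 29 percentage points with 24 per group (90.5% − 61.3%).

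**Conclusion.** The concern holds in a limited form. The equivalence label is wrong. The sized hypothesis (difference above 0.2) is stricter than the stated one (difference above zero), with observed thresholds of about 0.55 and 0.35 at 30 per group. Enrolment of 30 per group suits plain superiority, at about 90% power with 24 completers. It does not deliver the 90% of the chosen row for the margin claim, where power is about 61% to 71%. The necessity aim goes beyond what a null result could support, because the interval would still allow a benefit larger than the plan's own bounds.

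These figures assume the plan's variance of 0.46 in both groups, a true difference of 0.64 where power is quoted, two-sided α = 0.05, and the normal approximation for power. They apply to whichever outcome the 0.64 describes.

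**What to change.** 1. **Sample size:** delete the reference to equivalence and describe the formula as superiority by a margin, if that is the claim kept.
2. **Assumption and Sample size:** state one and the same hypothesis, naming the outcome it applies to and the favourable direction. This is needed because lower is better on the ODI and VAS and higher is better on the fusion score.
3. **Background:** replace the necessity aim with evaluating whether the orthosis is superior to no orthosis.
4. **Conclusion rule:** add one sentence saying that failure to show superiority will be reported as inconclusive with its confidence interval, and not as evidence that the orthosis is unnecessary.

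Which superiority claim to make is the sponsor's choice, and it should be fixed before any outcome data are seen. Plain superiority fits the present enrolment but requires the formula and Table 1 to be redone without Δ. If Δ = 0.2 is kept, the protocol should justify it and restate the power as about 61% to 71%. Restoring 90% would need 50 analysed per group, or 50/0.8 = 62.5, so 63 enrolled per group.

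The wording changes cost nothing in patients or procedures; the price is a more modest permitted conclusion. Keeping the margin is not free: it means accepting a 29% to 39% chance of missing the assumed effect, or roughly doubling enrolment.

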### Assumption

It is assumed that the clinical outcome of patients wearing spinal orthoses after OLIF is superior to that of patients in the control group.

## Methods/design

This is a randomized controlled trial, with the aim of comparing the effects of spinal orthosis on the clinical outcomes of patients after OLIF. This study was approved by the Ethics Committee of the Fourth Clinical Medical School of Xinjiang Medical University and will be conducted in accordance with the *World Medical Association Declaration of Helsinki*. This study has been registered in the Chinese Clinical Trial Registry (Registration No.: ChiCTR2200059000). Before treatment, all patients should sign the informed consent form.

The evaluation and statistical analysis of the results of this study will be performed by professionals who are not involved in the grouping. The study flow is shown in Fig. 1. The patients will be randomized into two groups, that is, group A (those wearing spinal orthoses after surgery) and group B (those not wearing spinal orthoses after surgery; control group).

**Fig. 1 Fig1:**
[figure not shown]
Study flow chart. OLIF, oblique lumbar interbody fusion; VAS, visual analog scale; ODI, Oswestry disability index; BFS, Brantigan, Steffee, Fraser

The main outcome measures include the Oswestry disability index (ODI), visual analog scale (VAS), and Brantigan, Steffee, Fraser (BSF) to assess pain intensity [28]. The clinical outcomes of these patients will be assessed using ODI and VAS scores 1 day before surgery and 2 weeks and 3, 6, and 12 months after surgery, and BFS scores will also be assessed starting from 2 weeks after surgery.

### Recruitment

First, we will evaluate potential candidates and inform them of our study procedures. Eligible patients will be randomized into two groups after written informed consent is obtained from each patient. Treatment will be given accordingly to the patient group. Patient recruitment and grouping will be performed by physicians in the subject group.

### Sample size

Because this study is based on clinical application, it is difficult to calculate the sample size through pre-experiments according to the actual situation; thus, the sample size of this study was finally determined based on the previous relevant literature data. The sample size outcome effect size was obtained from the literature using the ODI and VAS scores [29]. The mean change of the ODI in group A was approximately 92%, and the mean change of the VAS was approximately 0–3 points, while the mean change of the ODI in group B was approximately 85%, and the mean change of the NRS was approximately 4–5 points. The sample size was calculated using the sample size formula of the quantitative equivalence experiment *n* = 2(*Z*_*α*_ + *Z*_*β*_)^2^*δ*^2^/(*D* − *Δ*)^2^, assuming that *α* = 0.05 and *D* = 2.09 − 1.45 = 0.64, *δ*^2^ = [(0.56 + 0.78)/2]^2^ = 0.46 was obtained from literature retrieval, different values of *β* and superiority bounds were selected to calculate the sample size matrix, as shown in Table 1, and finally *n* = 50 was selected; taking into consideration a 20% dropout, thus 30 cases should be enrolled to each group, a total of 60 cases in two groups.

**Table 1 Tab1:** Sample size matrix

*α*	*β*	*D*	*δ*^*2*^	*Δ*	*n*
0.05	0.2	0.64	0.46	0.2	38
0.05	0.2	0.64	0.46	0.3	63
0.05	0.1	0.64	0.46	0.2	50
0.05	0.1	0.64	0.46	0.3	84

This trial is to be conducted in the Second Spine Department of the Fourth Clinical Medical School of Xinjiang Medical University, and hospitalized patients who meet the inclusion criteria will be included in the study. Because of the large number of patients undergoing OLIF in this department, it is possible to recruit sufficient subjects within the prescribed time; thus, an insufficient sample size is highly unlikely. In addition, there are benefits for patients participating in the study to supplement the sample size (e.g., free professional consultation, postoperative functional exercise instruction, and postoperative care consultation).

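### Table 1's n = 50 is a per-group number but was used as the two-group total; on the selected row, 60 enrolled gives about 61% power after 20% dropout (71% with none), not 90%

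*Protocol article*

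**What the plan says.** All of this stands in the Sample size section of the protocol article unless another section is named.

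- The method is introduced with "The sample size was calculated using the sample size formula of the quantitative equivalence experiment", followed by n = 2(Zα + Zβ)²δ²/(D − Δ)².
- The inputs are given as "assuming that *α* = 0.05", "D* = 2.09 − 1.45 = 0.64" and a variance of 0.46, from an expression ending "0.56 + 0.78)/2]^2^ = 0.46 was obtained from literature retrieval".
- Four combinations are tabulated: "different values of *β* and superiority bounds were selected to calculate the sample size matrix". Table 1 lists n = 38, 63, 50 and 84. The only row with n = 50 reads "0.05 0.1 0.64 0.46 0.2 50" (α, β, D, δ², Δ, n).
- With n = 50 selected, the enrolment follows: "taking into consideration a 20% dropout, thus 30 cases should be enrolled to each group, a total of 60 cases in two groups".
- The next paragraph assures the reader that a shortage of subjects is improbable because the department operates on many such patients.
- The Assumption section states the hypothesis as superiority and mentions no margin: "It is assumed that the clinical outcome of patients wearing spinal orthoses after OLIF is superior to that of patients in the control group".
- The Dropout or loss to follow-up section removes the data of withdrawn or terminated subjects from the final analysis.

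The text never says whether n in Table 1 is per group or for the whole trial.

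**The concern.** The step from 50 to 60 works only if 50 is the number for both groups together: 50 × 1.2 = 60, split into 30 and 30. But a formula for comparing two means with a leading factor 2 gives the number in one group. If n is per group, the trial enrols about half of what its selected row requires, before any dropout.

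The trial is meant to judge whether an orthosis is needed after this operation. A reader who believes the selected row's 90% would give a null result more weight than the design supports, and could take it as evidence that the orthosis is unnecessary.

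The label adds to the difficulty. The formula is attributed to an equivalence experiment, Δ is called a superiority bound, and the hypothesis is superiority with no margin. The reader cannot easily tell which claim the 60 patients are meant to support.

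**Working it through.** **Inputs (Sample size section and Table 1):** α = 0.05, D = 0.64, δ² = 0.46, Δ = 0.2 or 0.3, β = 0.2 or 0.1, dropout 20%, 30 enrolled per group. Sidedness is not stated, so both versions were tried.

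**Step 1. Reproduce Table 1 as printed.** n = 2(Zα + Zβ)² × 0.46/(0.64 − Δ)², with two-sided Zα = 1.96 and Zβ = 0.8416 or 1.2816:

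| β | Δ | n, unrounded | Rounded up | Table 1 |
|---|---|---|---|---|
| 0.2 | 0.2 | 37.3 | 38 | 38 |
| 0.2 | 0.3 | 62.5 | 63 | 63 |
| 0.1 | 0.2 | 49.9 | 50 | 50 |
| 0.1 | 0.3 | 83.6 | 84 | 84 |

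All four match. With one-sided Zα = 1.645 the formula gives 30, 50, 41 and 69, which does not match. The table therefore rests on 1.96.

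**Step 2. Per group or total?** The variance of a difference between two group means, with n in each group, is 2δ²/n. That is the source of the factor 2, so n is the size of one group.

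The variance input supports this. The printed expression [(0.56 + 0.78)/2]² equals 0.4489, not 0.46. The mean of the two squares does round to 0.46: (0.56² + 0.78²)/2 = (0.3136 + 0.6084)/2 = 0.461. If 0.56 and 0.78 are the SDs of the two groups, which the text does not say, then 2δ² = 0.92 is simply the sum of the two group variances. The 2 then belongs to the variance of the difference and is not a count of groups.

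**Step 3. Power of the planned enrolment on the selected row.** Power = Φ[(D − Δ)/√(2δ²/n) − 1.96], with D − Δ = 0.44 and 2δ² = 0.92. After 20% dropout, 30 × 0.8 = 24 per group remain.

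- n = 24: 0.44/√(0.92/24) − 1.96 = 0.287, power 61% (t-based 60%)
- n = 25: power 63% (t-based 61%)
- n = 30: 0.44/√(0.92/30) − 1.96 = 0.553, power 71% (t-based 70%)
- n = 50: power 90%

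**Step 4. Enrolment the selected row would need.** 50/(1 − 0.20) = 62.5, so 63 per group and 126 in total. The cruder 50 × 1.2 gives 60 per group and 120 in total. The plan has 60 in total.

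**Step 5. Sensitivity on the selected row.**

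- Variance 0.4489 instead of 0.46: 62% at 24 per group, 72% at 30.
- One-sided 0.05: 73% at 24, 81% at 30.
- No margin (Δ = 0), which is a different claim: n = 2 × 10.507 × 0.46/0.64² = 23.6, so 24 per group. Power at 24 is 90% (t-based 89%).

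**The case against.** **50 might really be a total.** Without the factor 2, the selected row gives 24.97, or 25 per group and 50 in all, so the 2 may have been read as the number of groups. That would explain the slip but does not justify it: with δ² as the variance of single patients, 25 per group has 63% power on that row.

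**The trial may be adequately powered for the hypothesis it states.** This is the strongest counter-argument, and part of it stands. The Assumption section names no margin, the Statistical analysis section describes no test against one, and with Δ = 0 the same inputs give about 89–90% power at 24 per group. A reader might therefore infer from the shortfall that the trial cannot detect the assumed difference at all. The documents do not support that. What they support is that the selected row is not delivered. The calculation did, however, use superiority bounds and choose Δ = 0.2, so the 90% cannot be moved to a margin-free claim without saying so.

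**The shortfall can be overstated.** About 60% belongs to 24 evaluable per group; 30 per group with no dropout gives 71%. Calling a null result a coin-flip also goes too far. Under the assumed effect, the chance of missing superiority by more than 0.2 is about 39% at 24 per group and 29% at 30.

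**The label is minor.** Calling the formula one for equivalence changes no number, and the text itself calls Δ a superiority bound. This is a wording fault.

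**Conclusion.** The error is established from the Sample size section alone. Table 1 gives per-group numbers, and the selected 50 was used as the total for both groups. On that row the power is about 61% after the planned dropout and about 71% with none. No variant tried with the 0.2 margin reaches 90% at the planned enrolment. Nor does 30 per group reach even the smallest entry in Table 1, which is 38.

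The figures rest on the plan's own D = 0.64 and δ² = 0.46, on Zα = 1.96 as implied by the table, and on losing 20% from each group. They are only as good as D, which the section does not tie to an outcome: 2.09 and 1.45 correspond to neither the ODI changes nor the pain ranges quoted beside them. The same limit applies to the margin-free 89–90%.

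The number is wrong as written and should be corrected. It does not follow that the margin should be deleted so that 60 becomes sufficient. The Trial status section dates recruitment from April 1, 2023, so that change would fit the claim to a sample already chosen, after the stated start.

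**What to change.** In the Sample size section:

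1. State that n in Table 1 is per group, based on two-sided α = 0.05.
2. State that the selected row needs 50 evaluable per group (126 enrolled at 20% dropout). State also that the planned 60 gives about 60% power for Δ = 0.2 with 24 evaluable per group, and about 71% if nobody drops out.
3. Remove the assurance that too small a sample is improbable. It concerns recruitment, but beside this calculation it reads as a statement about adequacy.
4. Replace the equivalence label with superiority by a margin.
5. As supplementary information only, the plan may add that the same inputs with Δ = 0 give about 89–90% power at 24 per group. Dropping the margin would change the claim from better by more than 0.2 to better than zero. It would need its own justification and disclosure as an amendment.

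The cost of items 1 to 4 is amended wording and a less favourable stated power. They require no change to enrolment.
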